##### Fecal microbiota analysis

The microbial composition will be determined through the use of Shallow Shotgun Metagenome sequencing [46, 47]. In this context, participants will bring to the hospital a stool sample collected at home in the first, third, and fourth assessments. The samples will be placed in a DNA/RNA Shield Fecal collection tube from Zymo Research, which is appropriate for the collection of a microbial snapshot of the sample, thus ensuring the safety, readinees for transport, and stability of the samples at ambient temperature. Samples will be frozen after reception for longer-term storage. Subsequently, DNA will be extracted from the stool samples using the ZymoBIOMICS DNA Miniprep Kit (Zymo Research, USA). Libraries will be constructed and analyzed for DNA samples that meet the requisite quality standards. The qualified libraries will be sequenced with the Illumina PE150 (5 G raw data per sample). The ulterior analysis will include species annotation with Kraken [48], the relative abundance of different species at different taxonomic levels, dimensionality reduction analysis based on species abundance and on the Bray–Curtis dissimilarity of species abundance, sample clustering analysis and anosim analysis, all based on species abundance, metastat [49] and LEfSe analysis [50] on inter-group differential species.

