**Methods:**

Twenty-eight participants (14 females), aged 18 to 50 years, will undergo sleeve gastrectomy surgery. They will be randomly allocated into a control group or a WBV training group. The WBV group will train three times per week with increasing intensities and duration ranging from 30 to 45 min over the 4-month training period. Measurements of body composition (dual-energy X-ray absorptiometry and peripheral quantitative computed tomography), physical fitness (muscular strength, agility, cardiorespiratory fitness, and balance), gait biomechanics, cardiometabolic markers, gut microbiota, quality of life, and physical activity levels will be collected at four different time points: (1) prior to the surgery, (2) 45 days post-surgery, (3) 6 months post-surgery, and (4) 18 months post-surgery.

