### Outcome variables

The primary outcomes will be (1) body composition, (2) results obtained from the adapted Bruce protocol, (3) basal metabolic rate, and (4) perceived quality of life. All the other variables will be considered as secondary variables. Both primary and secondary outcomes are explained in detail below.

All tests will be conducted in the GENUD-Lab, with the exception of the blood and stool collection, which will be performed at Clinico Lozano Blesa Hospital (situated a 5-min walk from the GENUD-Lab). The outcome variables will be assessed at four different time points (see Fig. 1 or 3). In each time point, participants will attend the laboratory on two different days, with less than a week between them. On each day, different variables will be collected, as detailed below.

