##### Dietary intake

A semiquantitative food frequency questionnaire [44] will be completed at the initial, third, and fourth assessments. The questionnaire comprises 133 items divided into nine food groups: (1) dairy products (15 items); (2) eggs, meat, and fish or seafood (23 items); (3) vegetables (18 items); (4) fruits (16 items); (5) legumes and cereals (11 items); (6) oils and fats (11 items); (7) pastries, cakes, or sweets (13 items); (8) a miscellaneous group (12 items); and (9) drinks (14 items). The questionnaire will refer to the preceding year and will be completed through an interview with a nutritionist. Each item included is accompanied by a description of the typical portion size. The participants will select the frequency of consumption between nine options (ranging from never to six or more times per day). Nutrient intake scores will be calculated using an ad hoc computer program designed for this purpose [45]. This will involve multiplying the frequency of consumption by the nutrient composition of a specified portion size. The selected frequency item will be converted to a daily intake. For example, if a response is 5–6 times a week, it will be converted to 0.78 servings per day. Portion size will be multiplied by the frequency of consumption in order to obtain the daily intake. The data extracted from this questionnaire will comprise total mean energy intake (kcal/day), macronutrients (protein, fat, and carbohydrates in g/day and % kcal of the total macronutrient energy distribution), alcohol (g and % kcal of the total macronutrient energy distribution), types of fatty acids (g/day), types of polyunsaturated fatty acids (PUFA) (n-3 and n-6) (g/day), and vitamins and minerals (mg or µg/day as corresponding to the nutrient in question).

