### Statistical methods

The Shapiro–Wilk test will be used to test for normality of the data while variance homogeneity and sphericity will be assessed with the Levene and Mauchly tests, respectively. To assess changes over time in the assessed outcomes, a repeated-measures ANOVA with Bonferroni correction will be used to assess the interaction between group (control group vs. WBV) and time (baseline vs. 2nd vs. 3rd vs. 4th assessments). In the absence of a normal distribution, data will be analyzed with the Wilcoxon test for within-group comparisons and the Mann–Whitney test for between-group comparisons using Bonferroni’s correction. To test for associations between variables, both correlations and linear regressions will be performed. The significance level will be set at 5%. Per-protocol and intention-to-treat analyses will be performed in order to account for the possible dropouts during the study. In the per-protocol analysis, we will include only the participants who attend at least 70% of the sessions and undergo the baseline and post-intervention outcome assessments. For the intention-to-treat analysis, we will consider all the participants who will undergo the baseline assessments and subsequently participate in at least one additional assessment following their group assignment will be considered.

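### Stool and diet are collected at three assessments (no T2), but the abstract states four for gut microbiota and the analysis model names four time levels without exception

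*Protocol article*

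**What the plan says.** The abstract's Methods paragraph states that "gut microbiota, quality of life, and physical activity levels will be collected at four different time points" and lists those points as "1) prior to the surgery, (2) 45 days post-surgery, (3) 6 months post-surgery, and (4) 18 months post-surgery". The opening of Outcome variables gives a general rule: "The outcome variables will be assessed at four different time points". It refers to Figures 1 and 3 and says that detail follows.

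The instrument sections are narrower. For stool, "participants will bring to the hospital a stool sample collected at home in the first, third, and fourth assessments". The food frequency questionnaire "will be completed at the initial, third, and fourth assessments". Neither has a second assessment.

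Statistical methods describes one repeated-measures ANOVA for changes over time in the assessed outcomes. It examines "the interaction between group (control group vs. WBV) and time (baseline vs. 2nd vs. 3rd vs. 4th assessments") and names no outcome to which a shorter time factor applies.

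The microbiota section also names its own methods: dimensionality reduction on Bray–Curtis dissimilarity, clustering, ANOSIM, Metastat and LEfSe. It does not say how assessments enter these methods. Outcome variables makes both microbiota and diet secondary.

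**The concern.** The abstract and the microbiota section cannot both be right about when stool is collected. A model whose time factor includes the 2nd assessment also has an empty cell for every participant on stool and diet. A repeated-measures ANOVA that needs complete rows would keep nobody if the four levels were taken literally.

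What is at stake is mainly what a reader believes can be learned. Objectives sets two aims: to describe the effect of sleeve gastrectomy and to assess the effect of whole-body vibration. T2 appears to be the last assessment before training starts. Outcomes measured at T2 can therefore show within-person change after surgery alone, and then change during training. From the abstract, a reader would expect that separation for gut microbiota, and it will not be available.

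**Working it through.** **Schedules side by side**

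| Place in the protocol article | Stool | Diet |
|---|---|---|
| Abstract, Methods | four points, including 45 days | not named |
| Outcome variables, opening | four points (general rule) | four points (general rule) |
| Fecal microbiota analysis / Dietary intake | T1, T3, T4 | T1, T3, T4 |
| Statistical methods, time factor | baseline, 2nd, 3rd, 4th (no exception) | baseline, 2nd, 3rd, 4th (no exception) |

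For stool, the conflict with the abstract is explicit. For diet, it is only with the general rule and the model.

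**Which interval is lost.** Study design puts T1 about 1 week before surgery, T2 at 7 ± 1 weeks after it and T3 at 24 ± 2 weeks.
- T1 to T2: 1 + 7 = about 8 weeks.
- T1 to T3: 1 + 24 = about 25 weeks. This is the first interval observed for stool and diet.
- The abstract's 45 days is 45/7 = 6.4 weeks, inside the T2 window of 6 to 8 weeks. The missing occasion is therefore the one the abstract names.

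**Where T2 sits relative to training.** Training lasts 16 weeks. Starting at T2 it ends at 7 + 16 = 23 weeks, inside the T3 window of 22 to 26 weeks. T2 as the last pre-training assessment is an inference from this timeline. On that reading, the T1–T3 change in the vibration arm covers about 8 weeks of surgery effect plus the training period, and the two cannot be separated within person.

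**What the model becomes.** With k = 2 groups and m time levels, the interaction has (k − 1)(m − 1) degrees of freedom: 3 for m = 4 and 2 for m = 3. The pairwise time comparisons subject to Bonferroni correction number m(m − 1)/2: 6 for m = 4 and 3 for m = 3. A three-level model, including Mauchly's test, is well defined on T1, T3 and T4.

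**Side check on sample size.** The inputs from Sample size are partial eta squared 0.06, correlation 0.5, alpha 5%, two groups and four measurements. Sphericity is assumed.
- f² = 0.06/0.94 = 0.0638 and λ = f²·N·m/(1 − ρ).
- m = 4, N = 24: λ = 0.0638 × 24 × 4/0.5 = 12.3 on 3 and 66 df, power 82.5%. At N = 22 power is 78.4%, so the stated 24 is reproduced.
- m = 3, N = 24, same inputs: λ = 9.2 on 2 and 44 df, power about 75%.

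The stated sample size is not in error.

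**The case against.** The strongest reply is that the schedule is not really in doubt. Two instrument sections independently give the same three occasions, and a specific statement governs a general one. The opening of Outcome variables can be read as saying that four assessment rounds exist, with detail by instrument to follow. Figure 3, which is not shown, may display that detail. An analyst holding T1, T3 and T4 data would use those three levels. Microbiota also has its own named methods, none of which needs a four-level time factor. Much of this stands, and it is why the point is minor. It does not repair the abstract, which names gut microbiota and lists the 45-day point. Nor does it supply the missing exception in Statistical methods.

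Three stronger readings are tempting and are not supported:
- **That no repeated-measures model can be run for these outcomes.** Only the four-level factor fails, and a three-level group-by-time model runs.
- **That the trial misstates its power for them.** With three measurements, power at 24 completers would be about 75% on the same inputs. But Sample size does not claim to power these secondary outcomes, so this figure contradicts nothing in the plan. It also has little meaning for methods such as ANOSIM or LEfSe.
- **That the treatment comparison is compromised.** Stool and diet are collected in both arms at T3 and T4, so the randomised contrasts remain valid.

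**Conclusion.** The inconsistency holds and is small. Stool and diet have 3 of the 4 assessments. The abstract is wrong about stool, and the time factor "time (baseline vs. 2nd vs. 3rd vs. 4th assessments") cannot be applied as written to either outcome family. Early post-surgery change, from surgery to about 7 weeks, will not be observed for them and should not be implied. No primary outcome, sample size or between-arm conclusion changes. The conclusion rests on the text alone. The statement that T2 precedes training is inferred from the stated weeks, and Figures 1 and 3 could not be checked. A three-occasion display in Figure 3 would support the instrument sections but leave the abstract and Statistical methods to be corrected.

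**What to change.** - **Abstract, Methods:** state that stool is collected at T1, T3 and T4, separately from the measurements taken at all four points.
- **Outcome variables:** qualify the general sentence so that stool and the food frequency questionnaire are shown as three-occasion measures.
- **Statistical methods:** specify a three-level time factor (T1, T3, T4) for diet and for any univariate microbiota summary, such as a diversity index. Compare the arms at T3 and T4 adjusted for the T1 value. Keep the methods already named in the microbiota section alongside this.
- **Reporting:** for these outcomes, describe T1–T3 change in the vibration arm as combining surgery and training, and attribute training effects only through the between-arm contrast.

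The contradiction itself requires only the schedule and time-factor corrections. The T1 adjustment is recommended because that value is already collected and can improve precision at no cost. The whole change is wording, with no new samples or visits and no restatement of power. If the abstract rather than the instrument sections reflects the intention, those sections must change instead, at the cost of a T2 stool sample. Nothing in the protocol suggests this.

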##### Hospital visits

Anthropometric parameters including body mass (SECA 813), height (Sayol stadiometer), waist circumference, hip circumference, and body mass index will be measured in the hospital. Vital signs including arterial blood pressure (Nellcor N5600) will also be recorded. Any chronic diseases and any acute disease that occurred during the 6 months preceding the onset of the study and any pharmacological treatment or nutritional supplement taken during the previous month will be recorded. Furthermore, all participants will undergo a blood extraction to evaluate the following parameters: hemogram and biochemistry, coagulation indicators, iron metabolism, liver enzymes, bone metabolic markers, C-reactive protein, and interleukin 6, in accordance with standard hospital procedures. In addition, tumor necrosis factor-alpha (TNF-α) levels will be quantified by enzyme-linked assay (ELISA) methodology (Quantikine High Sensitivity Human by R&D Systems, Minneapolis, MN, USA).

#### Day 2

##### Static balance—body sway

Participants will be required to stand barefoot on a three-axis force plate (Kistler Type 9260AA; Kistler Instruments Ltd, Hampshire, UK) in three different positions: with their feet parallel to each other, with one foot slightly in front of the other (semi-tandem), and with one foot directly in front of the other (tandem position) [51]. All tests will be conducted twice with the eyes open and twice with the eyes closed, each lasting for 30 s. The data will be processed and exported using the Kistler Mars software. The sway path (measured in millimeters) and velocity (measured in millimeters per second) will be used for further analysis.

##### Walking speed and step analysis

The participants will be requested to walk at their usual pace, with no footwear. To ascertain the time taken by the participants to complete the 6-m distance, photocells (Witty Gate Wireless Training Timer Photocells, Microgate, Italy) with a precision of 0.001 s will be placed at a distance of 6 m apart. Furthermore, the time taken to complete the 4-m distance will also be recorded manually. A two-step gait initiation protocol [52] will be employed with all participants commencing with their left leg. This ensures that the second step, which is performed with the right leg, is on a force plate (Kistler Type 9260AA; Kistler Instruments Ltd, Hampshire, UK) embedded in the walkway. The participants will complete five trials. During the follow-up visits, the tests will be performed at the participant’s normal speed (five attempts) and at the same speed as they performed the initial evaluation (mean of three attempts (excluding the fastest and slowest attempts)). A trial will be accepted if the speed is within a margin of ± 5% of the target speed. The Kistler Mars software will be used to process and export the data. The software provides more than 20 variables, which will be used to analyze the data. These include time parameters (stance, braking, and propulsion times), vertical component parameters, anterior–posterior component parameters, medio-lateral component parameters, and center of pressure parameters.

##### Timed Up and Go (TUG) test

The TUG [53] test will be performed twice with shoes. Participants commence the test seated on a chair and are instructed to stand up, walk a distance of 3 m, turn around, walk back to the chair, and sit down at their maximal speed but without running. The time taken to complete the test (s) will be recorded.

##### Five times sit-to-stand test

Participants will be asked to complete five repetitions of the sit-to-stand movement as rapidly as possible [54]. The time to complete the test (s) and power performed by each participant will be registered.

##### Health-Related Quality of Life (HRQoL) and pain questionnaires

The HRQoL questionnaire will be assessed with the Spanish version of the EUROQOL-5D-5L [55] and the SF-36 [56] questionnaires. The EUROQOL-5D-5L comprises five principal dimensions, 3 associated with physical capacity (mobility, self-care, and usual activities) and two with mental health (pain/discomfort and anxiety/depression). The visual analogic scale ranging from 0 to 100 will also be used. The SF-36 questionnaire encompasses eight health domains and is one of the most used questionnaires to assess HRQoL in patients who undergo BS [57].

##### Modified Bruce protocol

The modified Bruce protocol [58] will be performed on an instrumented treadmill (h/p/cosmos, Nussdorf–Traunstein, Germany). Participants will breathe through a low–dead space mask, with air sampled at 60 ml·min^−1^. Before each test, two-point calibrations of the gas sensors will be completed, using a known gas mixture (16% O_2_ and 5% CO_2_) and ambient air. The ventilatory volume will be calibrated using a 3-l (± 0.4%) syringe. The subjects will wear an instrumented portable electrocardiogram during all the tests (Cosmed Quark T12x). Gas exchange measurements will be registered breath-by-breath during the test and for 3 min of the recovery (Cosmed Quark, Rome, Italy). The objective of this test is to determine the V̇O_2_ peak (defined as the highest values obtained during the test) and the individual ventilatory anaerobic threshold (IAT), which is determined through visual assessment by an experienced sports and exercise physician.

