### Intervention

#### Randomization, allocation, and blinding

In order to ensure fairness, individuals who meet the eligibility criteria will be randomly assigned (1:1) to either a WBV group or a CG through the webpage https://www.sealedenvelope.com, taking sex into account (1:1). At the second visit, both groups will be provided with a brochure outlining the World Health Organization’s physical activity recommendations, as well as an ad hoc nutritional information sheet. A nurse will be responsible for recruiting all participants and will then direct them to the researchers, who will inform the participants of their group allocation, in accordance with the randomized order. Both groups will receive standard care, but the intervention group will also engage in an exercise intervention as outlined below. Given that the intervention will comprise WBV and that researchers will be involved in it, only the nurse and the statistician performing the statistics will be blinded. There is no foreseeable reason for the statistician to be unblinded to participant allocation.

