##### General information collection

All data and tests will be collected by sport scientists, with the exception of the food frequency questionnaire, which will be performed by a nutritionist, the exercise testing, which will be performed by a sports and exercise physician, and the collection of blood and stool samples, which will be performed by a nurse. The data collection process will include the following variables: sex, date of birth, mode of transportation to the research center (car, walking, or public transport), level of education, and dominant hand (left or right).

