##### The Western Ontario and McMaster (WOMAC) questionnaire, International Physical Activity Questionnaire (IPAQ), and Depression Anxiety Stress Scale questionnaire (DASS-21)

The three questionnaires will be completed by the participants with the assistance of the researchers in an interview format. The WOMAC questionnaire [42] will be used to ascertain the degree of knee and hip pain experienced by the participants. The short version of IPAQ will be used to determine the levels of physical activity and sitting time. The DASS-21 questionnaire will be employed to evaluate depression, anxiety, and stress in the Spanish version [43].

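### The ventilatory threshold, one of two stated results of a primary-outcome test, is read by eye by a physician outside the blinded set, although the recorded traces could be read under a code

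*Protocol article*

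**What the plan says.** Four sections of the protocol article bear on this point.

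- **Outcome variables.** The second of the four primary outcomes is "results obtained from the adapted Bruce protocol".
- **Modified Bruce protocol.** The test has two stated targets. VO2 peak is defined as the highest value reached. The other target, the individual ventilatory anaerobic threshold, is "determined through visual assessment by an experienced sports and exercise physician". The same section says that gas exchange is recorded breath by breath during the test and for 3 minutes of recovery.
- **General information collection.** Sport scientists collect most data. Among the exceptions is "the exercise testing, which will be performed by a sports and exercise physician".
- **Randomization, allocation, and blinding.** The reason for limited blinding is "Given that the intervention will comprise WBV and that researchers will be involved in it". The consequence is that "only the nurse and the statistician performing the statistics will be blinded".

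No section provides for a masked or coded reading of the threshold.

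**The concern.** A threshold placed by eye on gas-exchange curves is a judgement. If the person making it knows the arm, or knows which visit the trace comes from, expectation can move the reading. The article's abstract declares that expectation: the vibration group should improve more. Blinding the statistician does not help, because any shift is already in the recorded value when the analysis begins.

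This is not a detail left out of a condensed article. The article states who is blinded, with the word 'only', and states how the threshold is obtained. Taken together, these two statements fix an unmasked reading for part of a primary outcome. In a trial of 28 participants, a modest systematic shift in one arm could be mistaken for a training effect on the threshold.

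**Working it through.** **1. Is the threshold part of a primary outcome?** Yes. The Outcome variables section lists the Bruce-test results without singling out one of them, and the Modified Bruce protocol section names two: VO2 peak and the threshold.

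**2. Is it a judged reading?** Yes for the threshold, which is assessed visually. No for VO2 peak, which is the highest recorded value.

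**3. Is the reader blinded?** Not by plan. The blinded set is the nurse and the statistician. The reader is a sports and exercise physician, who is neither.

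**4. Does the stated reason cover this reading?** No. That researchers are involved in the training explains why participants and trainers cannot be masked. It gives no reason why a stored trace must be read with the arm or visit known. Because the signal is recorded breath by breath, it can be read later, apart from the test session.

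**5. How large could the effect be?** The documents give no reader error, repeatability or bias for the threshold, so the size cannot be derived from them. The following is an illustration under stated assumptions.

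*Number per arm.* The article's 12 per group reproduces. With partial eta squared 0.06, f² = 0.06/0.94 = 0.0638. For the within-between interaction, λ = f²·N·m/(1 − ρ) = 0.0638 × 24 × 4/0.5 = 12.26, with 3 and (24 − 2) × 3 = 66 degrees of freedom. Power is 0.825 at N = 24 and 0.784 at N = 22, so 24 is the smallest even total that reaches 80%.

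*Illustrative test.* A two-sided two-sample t test on change at 5%, with no true effect and a reader shift of δ SD of change in one arm. The noncentrality is δ·√(n/2). With n = 12 there are 22 degrees of freedom and the critical value is 2.074.

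| Assumed shift δ (SD of change) | Noncentrality, n = 12 | Rejection rate, 12 per arm | Rejection rate, 14 per arm |
|---|---|---|---|
| 0 | 0 | 5.0% | 5.0% |
| 0.1 | 0.245 | 5.6% | 5.8% |
| 0.2 | 0.490 | 7.6% | 8.0% |
| 0.3 | 0.735 | 10.8% | 11.9% |
| 0.5 | 1.225 | 21.6% | 24.7% |

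A shift of 0.1 SD hardly matters; a shift of 0.5 SD would matter a great deal. Nothing in the documents says where in this range, if anywhere, the reader would fall.

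**The case against.** The strongest reply is that the issue is narrow and its size unknown. It touches one of two results of one of four primary outcomes, and the exercise programme's stated main aim is bone and lean mass. The table rests on shifts with no anchor in the documents and on a simple t test, whereas the plan is a repeated-measures ANOVA of the group-by-time interaction over four assessments with Bonferroni correction. All of this stands, so the figures show scale only and are not this trial's error rate.

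A reader might also infer several stronger things that the documents do not support:

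- **That the trainer reads the threshold.** Training is led by a sports scientist, and nothing says the physician delivers it. The article does not say that the physician is told the arm either; it says only that the physician is not among those blinded.
- **That the whole Bruce outcome is affected.** VO2 peak is not read by eye. Effort and encouragement during testing could influence it, but coded reading would neither cause nor cure that.
- **That the questionnaires have the same avoidable flaw.** WOMAC, IPAQ and DASS-21 are completed "with the assistance of the researchers in an interview format". They are secondary outcomes, and participants know whether they trained. Self-completion might reduce interviewer influence but would not blind the answers.
- **That masking is free or complete.** It takes some work, and a physician who ran a test may recognise its trace among only 28 participants.

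None of these limits supplies a reason for leaving the reading unmasked.

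**Conclusion.** The point holds in a narrow form. A visually judged component of a primary outcome is assigned to a reader outside the blinded set, and the stated reason for limited blinding does not extend to reading recorded traces. This follows directly from the article's own statements and needs no numerical assumption.

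The size of the consequence is not established. The rates of 7.6%, 10.8% and 21.6% depend on assumed shifts of 0.2, 0.3 and 0.5 SD of change, 12 per arm and a t test on change. The conclusion is that an avoidable source of detection bias should be removed, not that the trial's result on fitness would be invalid.

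**What to change.** In both the blinding section and the Modified Bruce protocol section, state that the gas-exchange files are exported under a random code with participant, date, visit and arm removed, and that the physician determines the threshold from the coded files, in random order, without knowledge of allocation. If threshold values are needed after T3, before all files are available, state in advance which reading enters the final analysis, so that no trace has two candidate values without a rule.

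The cost is a little recoding work and later availability of the threshold values. No visit, test or treatment changes. Masking remains partial if the reading physician also ran the test and recalls it. A second reader unaware of allocation would be cleaner where one is available, but the improvement does not depend on it.
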